## **9.2 Screening Visit 2 (within 60 days of Day 1, pre-treatment phase)**

- Physical and neurological examinations
- MDS-UPDRS (morning assessment)
- Screening inclusion/exclusion criteria
- Vital signs (HR, BP, RR and T)
- Weight (morning assessment)
- ECG
- For female participants of child bearing potential, urine pregnancy test if applicable
- Routine blood collection
- Lumbar puncture (up to 20 mL) (morning assessment)
- CSF collection enzyme activity & ELISA antibody panels
- CSF ambroxol collection
- Adverse events review
- Concomitant medication review

## **9.3 Telephone Visit 1 (within 3 days of Visit 2)**

- Adverse events review
- Concomitant medication review

## **9.4 Treatment Phase - Visit 3 Day 1 (within 60 days of Visit 1 & 2)**

- Physical and neurological examinations
- MDS-UPDRS (morning assessment and pre-dose)
- Vital signs (HR, BP, RR and T), (pre-dose and 1 hour post IMP administration and prior to discharge)
- Weight (morning assessment)
- ECG (pre-dose and 1 hour post for each IMP administration)
- For female participants of child bearing potential, urine pregnancy test if applicable (pre-dose)
- Urine collection (morning assessment and pre-dose)
- Dosing on site, IMP Administration - Day 1 to day 186 (inclusive)
- Dispensing 3 months' supply of IMP to participant
- MoCA Cognitive assessment (morning assessment and pre-dose)
- NMSS and NMS Questionnaire
- Adverse events review
- Concomitant medication review

- Participants are instructed to self-administer 60 mg TID at day 1 to day 7
- Participant can be discharged and instructed to take the remaining daily dose(s) at home as soon as all other protocol procedures are completed.

#### **9.5 Telephone Visit 2 (within 3 days of Visit 3, day 1)**

- IMP compliance and dosing instructions
- Adverse events review
- Concomitant medication review

#### **9.6 Telephone Visit 3 (pre-dose escalation 2, within 3 days before day 8)**

- IMP compliance and dosing instructions
- Adverse events review
- Concomitant medication review

#### **9.7 Dose Escalation 2 (day 8)**

- Participants are instructed to self-administer 120 mg TID on day 8 to day 14.

#### **9.8 Treatment Phase - Visit 4 (within 3 days after dose Escalation 2, day 8)**

- Physical and neurological examinations
- Vital signs (HR, BP, RR and T)
- Weight (morning assessment)
- For female participants of child bearing potential, urine pregnancy test if applicable (pre-dose)
- Urine collection (morning assessment and pre-dose)
- Routine blood collection
- Blood collection
- Collecting IMP package (pill count only)
- Blood collection enzyme activity & ELISA antibody panels
- Blood ambroxol collection
- Urine collection (morning assessment and pre-dose)
- Dosing on site, IMP Administration - Day 1 to Day 186 (inclusive) if applicable
- IMP compliance and dosing instructions
- Adverse events review
- Concomitant medication review

#### **9.9 Telephone Visit 4 (pre-dose escalation 3, within 3 days before day 15)**

- IMP compliance and dosing instructions
- Adverse events review
- Concomitant medication review

#### **9.10 Dose Escalation 3 (day 15)**

- Participants are instructed to self-administer 180 mg TID on day 15 to day 21

#### **9.11 Telephone Visit 5 (post-dose escalation 3, within 3 days after day 15)**

- IMP compliance and dosing instructions
- Adverse events review
- Concomitant medication review

**9.12 Telephone Visit 6 (pre-dose escalation 4, within 3 days before day 22)**

- IMP compliance and dosing instructions
- Adverse events review
- Concomitant medication review

**9.13 Dose Escalation 4 (day 22)**

- Participants are instructed to self-administer 300 mg TID on day 22 and continue to day 28

**9.14 Telephone Visit 7 (post-dose escalation 4, within 3 days after day 22)**

- IMP compliance and dosing instructions
- Adverse events review
- Concomitant medication review

**9.15 Telephone Visit 8 (pre-dose escalation 5, within 3 days before day 29)**

- IMP compliance and dosing instructions
- Adverse events review
- Concomitant medication review

**9.16 Dose Escalation 5 (day 29)**

- Participants are instructed to self-administer 420 mg TID on day 29 to day 186

**9.17 Telephone Visit 9 (post-dose escalation 5, within 3 days after day 29)**

- IMP compliance and dosing instructions
- Adverse events review
- Concomitant medication review

**9.18 Treatment Phase - Visit 5 - Day 93 (+/- 14 days, treatment phase)**

- Physical and neurological examinations
- MDS-UPDRS (morning assessment and pre-dose)
- Vital signs (HR, BP, RR and T)
- Weight (morning assessment)
- For female participants of child bearing potential, urine pregnancy test if applicable, if applicable (pre-dose)
- Routine blood collection
- Blood collection enzyme activity & ELISA antibody panels
- Blood ambroxol collection
- Urine collection (morning assessment)
- Dosing on site, IMP Administration - Day 1 to Day 186 (inclusive) if applicable
- Dispensing 3 months' supply of IMP
- Collecting IMP packaging

- Adverse events review
- Concomitant medication review

### **9.19 Telephone Visit 10 (within 5 days of Visit 5)**

- IMP compliance and dosing instructions
- Adverse events review
- Concomitant medication review

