## 1. Summary

This is a proof of concept investigational medicinal product (IMP) study to investigate the safety, tolerability and pharmacodynamic effects of the Glucocerebrosidase (GCase) enhancing chaperone ambroxol in Parkinson disease (PD) participants with and without Gaucher gene (*GBA*) mutations. Twenty participants will be recruited in total, 10 with a *GBA* positive status and 10 with a *GBA* negative status. Each participant will orally self-administer ambroxol (ambrosan) at 5 intra-participant dose escalations at 60 mg TID (day 1-7), 120 mg TID (day 8-14), 180 mg TID (day 15-28), 300 mg TID (day 22-28) and 420 mg TID (day 29-186).

Participants will be subjected to clinical and laboratory assessments to assess the safety, tolerability and pharmacodynamic effects of ambroxol on blood and CSF biomarkers. Lumbar punctures will be performed to assess the penetration of ambroxol into the cerebrospinal fluid (CSF) through the blood-brain barrier (BBB) in the central nervous system (CNS) and the effects of ambroxol on GCase activity. Biomarkers and GCase activity markers will be assessed through the visits.

Each participant will undergo 7 hospital visits and up to 12 telephone visits. Hospital visits will include 2 screening appointments within 60 days of the Day 1 hospital visit (at which participants will receive the first dose of ambroxol), followed by a visit within 3 days of the second dose escalation, Day 93 (month 3), Day 186 (month 6) and an end of study follow up/early termination visit at Day 279 (month 9). Participants will receive a telephone call to record any adverse events in between hospital visits after screening visit 2, visit 3, the first dose, between 1-3 days before and after each dose escalation (day 1, 8, 15, 22 and 29), between day 93 and day 186, between day 186 and day 279 and a final telephone call within 5 days of the day 279 hospital visit if an optional lumbar puncture (LP) is undertaken. Please refer to Appendix 1 for the detailed schedule of events.

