We have reviewed the above animal, non-human primate and patient data and selected the 1260 mg/day dose to ensure efficacy in target engagement in the CNS, and detection in the CSF. The data indicate that a lower dose may not penetrate the CNS, or induce an effect necessary to enhance glucocerebrosidase activity.

Because there have been a small number of case reports of anaphylaxis associated with the IMP (and to ensure against other unreported or idiosyncratic side effects) we have opted for a regimen which includes 5 intra-participant dose escalations, 7 dedicated study visits, 10 telephone visits over the 6 months of IMP administration. For the same reason safety blood tests, clinical examination, ECGs and recording of AEs and concomitant medication are included at each study visit. Because a mild uricosuric effect was also reported in a recent clinical trial and in previous studies, serum urate will also be monitored (Narita et al., 2016 & Oosterhuis et al., 1993). The protocol also includes carefully thought-out and stringent stopping, withdrawal, termination and an additional intra-participant dose

escalation stopping criteria to ensure participant safety is not compromised throughout the course of the study.

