### 8.6.7 Lumbar Puncture (LP)

The LP procedure will be undertaken using aseptic technique as part of a morning assessment. The CSF collection should be performed using a small calibre atraumatic needle (e.g. 22 or 24 gauge Sprotte needle). During the procedure local anaesthetic will be used. The CSF will be collected using the traditional gravity drip method. Up to 20 mL (5-6 teaspoons) of CSF will be taken for analysis and storage, please refer to the latest laboratory manual for sample collection, processing transport and analysis.

After the LP procedure the participant must lay down (rest) for a minimum of 1 hour. The participant will be contacted by the research team within 5 days of the procedure to assess any adverse events or concomitant medication and advise the participant accordingly as part of the telephone visit. Participants will be advised to remain well hydrated, and to perform light activities for the next 48 hours.

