#### 8.6.7.1 Lumbar Puncture Restrictions

There are no restrictions to the study except the use of warfarin and other anticoagulants as described in the inclusion criteria and the requirements for a fasting CSF samples. Each participant must provide a fasting CSF sample for each LP procedure at the following visits: screening visit 2, visit 6 (day 186) and an optional LP at visit 7 (day 279). Participants are required to fast for a minimum of 4 hours before the LP procedure (no food except water).

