### 10.16 Assessment of Compliance and Adherence

The participants will be instructed to return all (used and un-used) IMP packages at each clinic visit for compliance check. The returned IMP will be collected from the CI/PI or the PI-delegated member of the research team from the participant at Visit 5 (day 93) and Visit 6 (day 186). The returned IMP will be counted to assess compliance in addition to telephone visits 2-10 where IMP compliance will be assessed.

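### Telephone visit 10 falls straight after visit 5, leaving 88 to 92 days at the top dose with no scheduled contact; moving it to about day 139 is a cheap improvement

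*Protocol*

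**What the plan says.** - **Purpose of the calls.** Section 1 (Summary) states: "Participants will receive a telephone call to record any adverse events in between hospital visits". Among the timings it lists are "between day 93 and day 186, between day 186 and day 279".
- **Timing of call 10.** Section 9.19 is headed "Telephone Visit 10 (within 5 days of Visit 5". Appendix 1 shows the call on days 94–98, and the next contact is visit 6 on day 186.
- **What visit 5 contains.** Section 9.18 lists examinations, bloods, the second dispensing, collection of packaging, and review of adverse events and concomitant medication. It lists no lumbar puncture and no compliance or dosing-instruction item. The last dose step is day 29 (section 9.16).
- **Five-day follow-up after a lumbar puncture.** Section 8.6.7 says "The participant will be contacted by the research team within 5 days of the procedure". Section 8.6.7.1 places the punctures at "screening visit 2, visit 6 (day 186) and an optional LP at visit 7 (day 279".
- **Compliance.** Section 10.16 counts returned product at visits 5 and 6 and adds "telephone visits 2-10 where IMP compliance will be assessed".
- **Monitoring as described in the rationale.** Section 2.2 speaks of "7 dedicated study visits, 10 telephone visits over the 6 months of IMP administration" and says "safety blood tests, clinical examination, ECGs and recording of AEs and concomitant medication are included at each study visit".

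**The concern.** Every other call has an evident reason for its date. Calls 2 to 9 follow the first dose or sit around the dose steps, and calls 1, 11 and 12 follow a visit with a lumbar puncture. Call 10 follows a visit with neither, and repeats an adverse event and medication review made one to five days before.

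The longest stretch of dosing, at the highest dose and 21 tablets a day (section 10.7), then has no planned contact until the visit at which dosing ends. A tolerability problem or a lapse in adherence that starts after call 10 is first asked about at visit 6, when it can be recorded but no longer corrected. Section 10.7 lets the investigator step a participant back to the last tolerated dose, but in this interval that depends on the participant getting in touch.

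**Working it through.** **Inputs** (section 9 and Appendix 1): call 9 on days 30–32; visit 5 on day 93 ± 14 (days 79–107); call 10 one to five days after visit 5 (nominally days 94–98); visit 6 on day 186 ± 14 (days 172–200); 420 mg three times daily from day 29 to day 186.

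**Gap as scheduled**

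- Time at the top dose: 186 − 29 + 1 = 158 days.
- Scheduled contacts in that time: call 9, visit 5, call 10 and visit 6. Two of the four fall within days 93–98.
- Call 10 to visit 6, nominal: 186 − 98 = 88 to 186 − 94 = 92 days, which is 56% to 58% of the 158 days.
- Shortest across the windows: 172 − (107 + 5) = 60 days.
- Longest across the windows: 200 − (79 + 1) = 120 days.

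**Gap with call 10 at day 139**

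| Interval | Nominal | Longest across windows |
|---|---|---|
| Visit 5 to call 10 | 139 − 93 = 46 | 139 − 79 = 60 |
| Call 10 to visit 6 | 186 − 139 = 47 | 200 − 139 = 61 |

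The gap from call 9 to visit 5 does not change: 93 − 32 = 61 to 93 − 30 = 63 days nominal. It would then be the longest nominal gap at this dose.

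**Section 2.2 against the schedule**

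- Calls during dosing: calls 2 to 10, so 9, in agreement with section 10.16. The stated 10 is reached only by adding call 1 (before dosing) or call 11 (days 187–191, after the last dose).
- Clinic visits during dosing: visits 3 to 6, so 4. Seven is the correct whole-study total.
- ECG: visits 1, 2, 3, 6 and 7, so 5 of 7. Section 8.6.6 itself refers only to selected visits.
- Routine bloods: visits 1, 2, 4, 5, 6 and 7, so 6 of 7. The one without is visit 3, the first-dose day, after two screening sets.

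**The case against.** **No rule is broken.** Days 94–98 do lie between day 93 and day 186, section 9.19 and Appendix 1 agree, and the protocol sets no maximum interval between contacts. This stands: a reader might infer a contradiction with the Summary, but there is none. What remains is a date that does little for the purpose the Summary gives.

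**Call 10 has a use where it is.** Visit 5 hands out the second three-month supply, section 9.18 lists no dosing check there, and call 10 provides one. This stands in part. The visit 5 pill count covers much of it. Appendix 1 also appears to carry a compliance check at visit 5: its compliance row has 12 marks, which fit calls 2 to 10 (9) plus visits 4, 5 and 6 (3). The columns of that row are displaced in the text available, so this is a reading and not a certainty.

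**The five-day window may be deliberate.** It is tempting to say it was carried over from the lumbar puncture rule. That is only an inference, and call 1, which also follows a puncture, uses three days.

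**Other routes exist.** Unscheduled visits are allowed (section 9.24), and participants must report misuse of the product (section 10.7) and overdoses with possibly related adverse events (section 10.9). True, but these depend on the participant raising the matter; a scheduled call asks.

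**The primary outcome is not shown to suffer.** Visit 6 gives the only required CSF sample on drug, and section 2.2 notes that the low end of the CSF ambroxol range in an earlier Gaucher disease study is at the limit of detection. A reader might infer that the contact gap puts the day 186 result at risk. The protocol does not support that. Blood ambroxol is taken at the same visit and returned product is counted, so a low CSF level can be read against both. A call 47 days earlier would not verify the last doses before the puncture.

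**Conclusion.** The point holds as a cheap improvement of minor weight. Call 10 adds little one to five days after a full visit, and leaves 88 to 92 nominal days (60 to 120 across the windows) at the maximum dose without scheduled contact. Placed at mid-interval, the same call would bring the longest gap after visit 5 down to about 47 nominal days, and to 61 instead of 120 at the extreme of the windows.

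The benefit claimed is earlier detection of tolerability or adherence problems, while something can still be done. The protocol gives no adherence or tolerability rates from which to put a number on it. The gaps count scheduled contact only and assume the visit windows as written.

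The statements in section 2.2 are inaccurate, but they sit in the rationale. Section 9 and Appendix 1 govern what is done, so correcting the text changes nothing in the conduct of the trial.

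**What to change.** 1. In section 9.19 and Appendix 1, move the existing call 10 to about day 139, keeping its content: compliance and dosing instructions, adverse events and concomitant medication.
2. In section 9.18, list the compliance and dosing-instruction item for visit 5.
3. As an accompanying text correction, reword section 2.2: 4 clinic visits and 9 calls during dosing; ECG at visits 1, 2, 3, 6 and 7; routine bloods at visits 1, 2, 4, 5, 6 and 7.

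The Summary and section 10.16 remain true as they stand. The cost is wording in four places, with no added visit, call or test. The early phone check after the second dispensing is lost, though the visit 5 pill count and the added item in section 9.18 largely replace it. The 61 to 63 day gap before visit 5 stays.

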### **9.20 Treatment Phase - Visit 6 - Day 186 (+/- 14 days)**

- Physical and neurological examinations
- MDS-UPDRS (morning assessment)
- Vital signs (HR, BP, RR and T)
- Weight (morning assessment)
- ECG
- Lumbar puncture (up to 20 mL) morning assessment
- For female participants of child bearing potential, urine pregnancy test if applicable (pre-dose)
- Routine blood collection
- Blood collection enzyme activity & ELISA antibody panels
- CSF collection enzyme activity & ELISA antibody panels
- Blood ambroxol collection
- CSF ambroxol collection
- Urine collection (morning assessment)
- Dosing on site, IMP Administration - Day 1 to Day 186 (inclusive), last day of dose
- Collecting IMP packaging
- MoCA cognitive assessment (morning assessment)
- NMSS and NMS Questionnaire
- Adverse events review
- Concomitant medication review

### **9.21 Telephone Visit 11 (within 5 days of Visit 6, day 186)**

- Adverse events review
- Concomitant medication review

### **9.22 End of Study/Early Termination Visit Follow Up Phase – Visit 7, Day 279 (+/- 30 days)**

- Physical and neurological examinations
- MDS-UPDRS (morning assessment)
- Vital signs (HR, BP, RR and T)
- Weight (morning assessment)
- ECG
- \*Optional lumbar puncture – if participant agrees to optional LP they will be followed up by a telephone call to assess any AEs and a concomitant medical review within 5 days of the visit.
- CSF collection enzyme activity & ELISA antibody panels if participant consents to the optional lumbar puncture procedure (if participant consents to LP)
- \*CSF ambroxol collection only if participant consents to optional lumbar puncture procedure (if participant consents to LP)

- \*\*Collecting IMP packaging, if early termination visit
- For female participants urine pregnancy test unless menopausal status is confirmed (if applicable)
- Blood collection enzyme activity, ELISA antibody panels
- Routine blood collection
- Urine collection (morning assessment)
- Collecting IMP packaging
- Adverse events review
- Concomitant medication review

### **9.23 Optional Telephone Visit 12, if participant consents to optional lumbar puncture (within 5 days of Visit 7, Day 279)**

- Adverse events review
- Concomitant medication review

### **9.24 Unscheduled Visits**

Unscheduled visits may be performed at any time during the study, whenever necessary to assess or to follow up on adverse events (AEs) or serious adverse events (SAEs) at the participant's request, or as deemed necessary by the Investigator.

If a participant wishes to withdraw from the study early, they will be invited to attend visit 7, day 279 (end of study visit/early termination visit) at that point prior to withdrawing from the study.

## **10. Investigational Medicinal Product (IMP) – Ambroxol**

### **10.1 Name and Description of IMP**

Ambroxol hydrochloride 60mg tablets (Brand Name: Ambrosan).

Each tablet contains 60 mg of ambroxol hydrochloride. The appearance is almost round and is cross-scored and the diameter 9.5 mm. Ambroxol contains the following excipients: lactose monohydrate, granulated microcrystalline cellulose, copovidone and magnesium stearate.

### **10.2 Mode of Action**

Ambroxol increases the clearance of mucus in the respiratory system by enhancing pulmonary surfactant production and stimulating ciliary activity improving mucociliary clearance and expectoration, and eases cough-like symptoms. Ambroxol decreases bronchial hyper-reactivity by increasing the secretion of immunoglobulin A (IgA) in bronchial mucus; it also shows antioxidant activity.

### **10.3 Source of IMP, Manufacture, Distribution and Storage**

Ambroxol hydrochloride 60mg tablets will be sourced by PRO.MED.CS Praha a.s. (ambroxol marketing authorisation holder) that are based in the Czech Republic within Europe.

## **10.4 Preparation and Labelling of Investigational Medicinal Product**

PRO.MED.CS Praha a.s. will send IMP shipments to the RFH Pharmacy Production Unit (MIA (IMP) holder) for re-packaging and re-labelling in accordance with EU GMP Annex 13. The latter will provide Qualified Person (QP) certification and will send the re-packaged and re-labelled IMP to the NHNN Pharmacy department for dispensing and storage for the study.

## **10.5 Storage and Handling of IMP at Site**

The IMP does not require any special storage requirements and will be stored at ambient conditions during transportation and while at sites. Guidance on handling temperature excursions is provided in the Summary of Drug Arrangements (SoDA) document.

## **10.6 Accountability of IMP(s)**

The Sponsor will provide guidance on the destruction of unused investigational product (eg, at the site). If destruction is authorised to take place at the study site, the investigator must ensure that the materials are destroyed in compliance with applicable environmental regulations, institutional policy, and any special instructions provided by the Sponsor and all destruction must be adequately documented. Further guidance will be provided in the SoDA. IMP shipping, receipt, storage and accountability arrangements for the site will be described in the Summary of Drug Arrangements (SoDA) document.

## **10.7 Treatment Schedule and Dosing Instructions**

Participants will be instructed to self-administer 5 intra-participant dose escalations at 60 mg TID (day 1-7), 120 mg TID (day 8-14), 180 mg TID (day 15-21), 300 mg TID (day 22-28) and 420 mg TID (day 29-186). The study drug should be administered with or without a meal and rinsed down with sufficient amount of fluid for each daily morning, afternoon and evening in accordance to the instructions provided by the Investigator.

On the first day of dosing, day 1, the study drug should be self-administered by the participant at the site as described above. The participant will undergo vital signs performed an hour after the first dose. Participants can be discharged and instructed to take the remaining daily dose(s) at home as soon the other protocol procedures are completed and will undergo vital signs clinical assessment before being discharged.

At all subsequent schedule visits, participants may self-administer the study medication on site and will be instructed to take the remaining daily dose(s) if applicable by the Investigator accordingly (especially on lumbar puncture visits) and will be discharged after the first dose if applicable.

On screening visit 2, visit 3 (day 1), visit 5 (day 93), visit 6 (day 186) and visit 7 (day 279), participants should not administer their standard of care PD medication until they have undertaken the UPDRS assessment and will be instructed by the PI or PI-delegated member of the research team, this is a standard of care procedure and the Investigator will instruct each participant.

During the course of the study, if a participant misplaces, incorrectly stores or uses the IMP outside the dosing instructions provided, the participant must notify the PI/PI-delegated member of the research team to assess whether replacements of the IMP is required.

| Dose Escalation Number | Day    | Ambroxol (Ambrosan) Dose and Frequency | Ambroxol (Ambrosan) Daily Dose (mg/day) | Number of 60 mg Tablets per Dose | Total Number of 60 mg Tablets Per Day |
|------------------------|--------|----------------------------------------|-----------------------------------------|----------------------------------|---------------------------------------|
| 1                      | 1-7    | 60 mg TID                              | 180                                     | 1                                | 3                                     |
| 2                      | 8-14   | 120 mg TID                             | 360                                     | 2                                | 6                                     |
| 3                      | 15-21  | 180 mg TID                             | 540                                     | 3                                | 9                                     |
| 4                      | 22-28  | 300 mg TID                             | 900                                     | 5                                | 15                                    |
| 5                      | 29-186 | 420 mg TID                             | 1260                                    | 7                                | 21                                    |

Dose reductions are not planned but may be permitted. The PI may allow a dose reduction if adverse symptoms have emerged since dose increase that are considered to be due to the increase, are not SAEs and do not require the participant to be withdrawn, and in the opinion of the PI and participant to warrant a reduction to the last tolerated dose level.

